### Plans to give access to the full protocol, participant level-data and statistical code

Access to the full protocol, participant-level data, and statistical code will be restricted and carefully controlled. Researchers interested in accessing these materials must submit a formal application, which will be subject to review by the Institutional Review Board (IRB) for local data processing. This process is designed to ensure the protection of sensitive information and maintain the integrity of the research. It is important to note that, in accordance with the decision of the data security board at the University of Frankfurt, no data can be shared outside of this controlled environment consisting of the study team in Frankfurt and selected members of the study team in Darmstadt.

### Composition of the data monitoring committee, its role and reporting structure

According to German law, no formal data monitoring committee is needed for a study without therapeutic intervention.

### Plans for communicating important protocol amendments to relevant parties (e.g., trial participants, ethical committees)

Protocol modifications will firstly be sent to the central and local ethics committees. Once changes are approved, currently enrolled patients will be asked to sign the newest version of the informed consent form accordingly.

## Dissemination plans

Study results will be communicated to the scientific community and general public via publications.

## Discussion

The SPEAK-SAFE study protocol presents a novel approach to utilizing Natural Language Processing (NLP)/multimodal methods for analyzing therapist-patient conversations in psychiatric care. This discussion addresses key aspects of the study design, potential challenges, and implications for future research and clinical practice.

The sensitive nature of the conversational data collected in this study necessitates robust privacy measures. Our study represents an initial feasible approach to this matter. Future research should further address these issues to optimize data collection while ensuring adequate implementation of data security. Collaboration with institutions like ATHENE will be instrumental in developing innovative and secure solutions for mental health research.

The integration of cutting-edge cybersecurity measures not only enhances the robustness of our data protection protocols but also sets a precedent for future studies in this field. This interdisciplinary approach, combining mental health research with advanced cybersecurity practices, paves the way for more secure and efficient data handling in sensitive research areas.

In addition to the challenges arising from the strict data protection guidelines, recording therapy sessions presents several technical challenges that could impact data quality. There are indications that the quality of the final results is more negatively affected by poor audio quality rather than computational issues (62). Background noise, variations in speech volume, and acoustic properties of the recording environment are crucial influencing factors which may affect transcription accuracy and overall data quality in non-laboratory settings (63). To mitigate these issues, we have implemented quality assurance strategies, including the use of high-quality recording equipment and careful placement of microphones. Nevertheless, some degree of data loss or inaccuracy may be unavoidable, potentially impacting the AI model's performance.

What accuracy should be expected from an AI-based suicide evaluation? Large language models demonstrate strong performance in detecting depression and suicide risk from clinical narratives, with recent real-world validation substantially informing expectations for psychotherapy transcripts. In a recent cross-sectional study of 100 admission notes from a psychiatric hospital, a German-fine-tuned Llama-2 model achieved 87.5% accuracy, 83.0% sensitivity, and 91.8% specificity in identifying suicidality status against expert ground truth, demonstrating robust performance across varied prompting strategies while preserving data privacy (64). To contextualize these capabilities, human interrater reliability in assessing mental health from dialogue provides an essential benchmark. Unstructured suicide risk assessment shows substantially lower concordance: psychotherapists demonstrate Gwet's AC₁ = 0.44 with only 58% identical risk classifications, while psychology students achieve AC₁ = 0.35 (65). Unstructured psychiatric diagnosis using clinical interviews yields *κ* = 0.24–0.43 (fair at best), compared to *κ* = 0.75 (substantial) when structured protocols guide assessment (66). This empirical gap is instructive: current clinical practice relies on unstructured judgment with relatively poor reliability, particularly for suicide risk estimation. Consequently, LLM-assisted assessment of suicidality in psychotherapy transcripts is already useful potentially when achieving only modest accuracy performance.

The dialogic nature of therapy sessions introduces complexities in transcription and analysis. Colloquialisms, pauses, overlapping speech, and non-verbal cues are integral to therapeutic communication but challenging to capture and analyze (67). Our multimodal approach aims to address these challenges by incorporating advanced speech recognition and sentiment analysis techniques. However, the nuances of therapeutic dialogue may still pose difficulties in accurate interpretation, necessitating ongoing refinement of our multimodal models.

The SPEAK-SAFE study utilizes both structured (questionnaires) and unstructured (conversation recordings) data. While structured data offers standardized, easily quantifiable information, unstructured data provides rich, contextual insights into patient-therapist interactions (68). Our decision to focus on conversational data stems from its potential to capture subtle linguistic markers of mental health states that may not be evident in structured assessments. Our aim is to predict occurring changes in the structured data, what we consider as ground truth, by using the rich, unstructured speech data.

A limitation of the current study design is the lack of long-term follow-up to assess the predictive accuracy of the NLP/multimodal model over time. This has been done so far by only few studies (36). While our approach provides valuable insights into immediate risk assessment, the dynamic nature of mental health conditions necessitates longitudinal evaluation. Future research should incorporate extended follow-up periods to validate the model's long-term predictive capabilities and assess its utility in tracking treatment progress.

The use of AI in mental healthcare raises important ethical considerations. Potential biases in NLP/multimodal models, particularly regarding cultural and linguistic diversity, must be carefully addressed (69). Moreover, the integration of AI-based tools in clinical decision-making necessitates a balance between technological assistance and human clinical judgment. Our study emphasizes the importance of human oversight in interpreting AI-generated insights, recognizing that these tools should augment rather than replace clinical expertise.

The SPEAK-SAFE study has significant potential to enhance mental health care. By providing clinicians with AI-assisted risk assessment tools, we aim to improve the accuracy and efficiency of suicide risk evaluation (34). This could lead to more timely interventions and personalized treatment strategies. However, the successful integration of such tools into clinical workflows requires careful consideration of user acceptance, training needs, and potential impacts on the therapeutic relationship.

Building on the SPEAK-SAFE study, future research should explore the application of our AI models to a broader range of mental health conditions. Additionally, investigating the integration of multimodal data, including physiological measures and social media activity, could enhance the model's predictive capabilities (13). Longitudinal studies examining the long-term impact of AI-assisted care on patient outcomes are also crucial for validating the clinical utility of this approach. We plan to augment our data collection with smartphone-based ecological momentary assessment (EMA) to allow outcome prediction.

In conclusion, the SPEAK-SAFE study represents a significant step towards leveraging AI in mental health care. While challenges remain in data collection, analysis, and ethical implementation, the potential benefits in improving risk assessment and patient care are substantial. Continued research and interdisciplinary collaboration will be essential in refining these approaches and translating them into clinical practice.

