With our study, we aim to fill this gap by applying recent advances in NLP and multimodal methods. Our goal is to help identify non-explicit content language patterns in clinical patients, which can serve as prognostic markers specifically for the German language. Thus, our primary aim is to assess the suicide risk in patients with depression, bipolar disorder, and psychotic disorders, such as schizophrenia, schizoaffective disorder and acute polymorphic psychotic disorder (according to ICD-10), as well as the psychopathological development (Clinical Global Impression, CGI). As a secondary outcome we want to assess the overall psychopathological condition of the patients. This includes standardized and validated questionnaires comprising the clinician's impression of the patients general psychosocial functioning (Global Assessment of Functioning, GAF), suicidal symptoms (Depressive Symptom Index—Suicidality Subscale, DSI-SS) and suicidality (Suicidal Scale of the Mini-International) as well as electronic health records (EHR) of the patient's psychopharmacological medication. Generally, the standardized text of the patient's EHR will be accessible for the text-based analysis. These will be supplemented by the standardized assessment through a clinician, which will be used as the gold standard for comparison with the AI analysis.

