### Outcomes

As part of an initial exploratory analysis, the assessment of psychopathology by treating physicians is to be compared with the evaluation by a computer model. Therefore, using intraclass correlation coefficients or t- tests, the hypothesis “There is no difference in the assessment of patients regarding the severity of illness and suicidality” will be tested.

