### Participant timeline

In-patients and out-patients will regularly be screened for participation eligibility. If the eligibility criteria are met and in consultation with their treating clinicians, patients will be informed about their study and will have at least one day to consider participation and sign the informed consent. The same procedure applies for clinicians who participate in the study, while they only must consent once for the recording of therapy sessions with several patients who gave informed consent. From the time point on where patients agreed to participate, up to five of their regularly held therapy sessions will be recorded. After the therapy session, patients and therapists will fill out questionnaires about the psychopathology of the patient (approx. 5 min. for each). They are asked to fill out the questionnaire on the same day the therapy session took place. Table 1 summarizes the procedure and when the respective questionnaires are used.

**Table 1 T1:** Content for the schedule of enrollment and participation.

TIMEPOINT	Enrollment	Informed Consent	Recording and Questionnaires				
	*−t2*	*−t1*	*t1*	*t2*	*t3*	*t4*	*t5*
	Ongoing	After confirmation by clinician	At least 1 week between each participation				
			Up to five therapy sessions can be recorded per participant				
			Questionnaires have to be filled out the same day as the recording				
*Study admission*							
Eligibility screen	X	X					
Consultation with the treating clinician	X						
Informed consent		X					
*Recording of therapy session*			X	X	X	X	X
*Patient reported outcomes (PRO)*							
*Beck’s Depression Inventory (BDI-II)*			X	X	X	X	X
*DSI-SS-Scale*			X	X	X	X	X
MINI C Suicidality Scale			X				
*Demographics, Diagnoses and Concomitant Medication*			X				
*Therapist Ratings*							
*Global Assessment of Functioning (GAF)*			X	X	X	X	X
*Clinical Global Impression (CGI)*			X	X	X	X	X
*Brief Psychiatric Rating Scale (BPRS)*			X	X	X	X	X

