### Data management

During the data collection phase, the raw audio recordings, patient data, and questionnaires will be collected. In this phase, only clinicians and student assistants from the University hospital in Frankfurt as well as one doctoral student from the Privatklinik [name] in Königstein are involved. The analysis of the data is conducted by the Ubiquitous Knowledge Processing (UKP) Lab at TU Darmstadt using natural language processing and multimodal methods and is mostly carried out in Darmstadt exclusively with pseudonymized data. The data accessed by the research group from TU Darmstadt will only have pseudonymized files and data without any personal information about the participants. The data analysis is complemented by a standardized assessment of the course by an independent board-certified psychiatrist or experienced assistant in psychiatry, serving as a “gold standard” for comparison with the AI analysis. Thus, the pseudonymized audio files are listened to and classified by a board-certified psychiatrist based on clinical features. The gold standard assessment covers three different areas. It consists of the BPRS as a broad psychopathology questionnaire, the five-stage severity item of the CGI-SS combined with an open question, asking the experts to briefly justify their rating within 2–3 sentences and the VTAS-R-Short Form, a five-item therapeutic alliance questionnaire (55).

The pseudonymized audio recordings will then be analyzed for acoustic and prosodic features using the open-source toolkit, openSMILE (56) and then transcribed to text with the freely available software WhisperX (57). Both datasets will then be analyzed on its own and later on fed to a multimodal neural network to generate a clinically relevant outcome score (e.g., suicidality prognosis score). Figure 1 shows an overview of our workflow.

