Tier 1: Unimodal Baseline Analysis. We will analyze each modality independently to establish baseline predictive performance before considering fusion. For the text modality, we will conduct two-way mixed-effects logistic regression with outcomes (diagnostic classification or severity degree) regressed on the fixed effects of model size and temperature, with random intercepts for participant and session. Effect sizes will be reported as odds ratios with 95% confidence intervals. For the acoustic modality, we will conduct mixed-effects linear regression using a reduced set of the most clinically relevant acoustic features selected *a priori* based on prior literature associations with depression and suicidality, including pitch variability, energy measures, MFCC and jitter as predictors of continuously scored clinical outcomes (e.g., severity scores from standardized rating scales) (60, 61).Tier 2: Factorial Interaction Analysis for 2 × 2 Design. For text-based predictions, we will formally test the 2 × 2 factorial design using mixed-effects ANOVA to partition variance according to main effects (model size, temperature) and their interaction. Specifically, we will model primary outcome (e.g., predicted depression severity) as a function of fixed effects for model size (GPT-OSS-120B vs. 20B), temperature (0.1 vs. 0.8), and their interaction (Model Size × Temperature), with random intercepts for participants and sessions to account for the hierarchical data structure. This approach allows us to determine whether inference strategy recommendations (conservative vs. liberal temperature) can be applied consistently across model sizes, or whether optimization differs by model choice. If a significant Model Size × Temperature interaction emerges, it would suggest that clinical deployment requires model-specific tuning. Conversely, absence of interaction would support unified recommendations applicable regardless of computational constraints. We will report partial eta-squared (*η*²p) effect sizes with 95% confidence intervals for each factorial term.Tier 3: Multimodal fusion and Late-Fusion Integration. To evaluate how textual and acoustic information combine for clinical prediction, we will employ a structured late-fusion approach. For each of the four 2 × 2 factorial conditions, we will generate separate predictions from the GPT-OSS models (text modality) and from a logistic regression model trained on acoustic features (acoustic modality). We will then integrate these predictions through weighted averaging, with weights determined via cross-validation (80% training, 20% held-out validation) on a stratified subset of sessions. This approach maintains interpretability—each modality's contribution can be quantified—and avoids the architectural complexity that would introduce uncontrolled hyperparameter flexibility incompatible with pre-registration.We will quantify multimodal benefit by comparing fusion performance (AUC, sensitivity/specificity at clinically relevant decision thresholds) against the best unimodal baseline. If fusion provides incremental improvement beyond single modalities, we will use mixed-effects logistic regression with interaction terms to test whether the fusion benefit depends on model size or temperature setting. This tests the hypothesis that acoustic information provides complementary information that enhances text-based predictions uniformly, or whether certain model configurations better leverage multimodal information.

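### Prognosis, course and change are stated aims, but every analysis target the protocol spells out is a same-session level or a diagnosis

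*Protocol article*

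**What the plan says.** **Aims.** The Objectives look for language patterns "which can serve as prognostic markers specifically for the German language". The primary aim there is assessment of suicide risk "as well as the psychopathological development (Clinical Global Impression, CGI". Data management describes a multimodal network "to generate a clinically relevant outcome score (e.g., suicidality prognosis score". The Discussion says "Our aim is to predict occurring changes in the structured data, what we consider as ground truth".

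**Analysis targets.**
- Outcomes: the hypothesis is "There is no difference in the assessment of patients regarding the severity of illness and suicidality", examined by intraclass correlation or t-test.
- Participant timeline, on the questionnaires: "They are asked to fill out the questionnaire on the same day the therapy session took place".
- Data management: the gold standard is rated from the recording itself. It consists of the BPRS, "the five-stage severity item of the CGI-SS combined with an open question", and a short alliance questionnaire.
- Statistical methods: the primary outcomes are diagnostic classification, suicidality detection and correlation of severity scores with clinical measures. Tier 1 models diagnosis or severity from text, and uses acoustic features "as predictors of continuously scored clinical outcomes (e.g., severity scores from standardized rating scales". Tier 2 gives predicted depression severity as its example. Tier 3 uses AUC, sensitivity and specificity.

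**Data that could serve the aims.** Table 1 schedules BDI-II, DSI-SS, GAF, CGI and BPRS at t1 to t5, at least one week apart. The section on assessment and collection of outcomes says that CGI global improvement is collected, and that the CGI-SS covers change in suicidality, re-anchored to the time since the last assessment.

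**The concern.** Prognosis needs a rating made after the speech sample. Change needs a comparison of the same patient at two times. A same-session comparison of levels supplies neither. Patients who are generally more ill will tend to have worse ratings at each of their sessions, so a score can agree well with session ratings by separating patients from one another, without registering when one patient gets worse or better.

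Separating patients is a legitimate result, but it is not the aim stated in the Discussion. If the plan is followed exactly, a good AUC or correlation would leave the prognosis and change aims unanswered, although the repeated ratings needed to address them in the short term are already on the schedule.

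**Working it through.** **1. Aims against targets.**
- Prognosis (Objectives, Data management) needs speech at one time and a rating at a later time. No tier names a later rating.
- Course (Objectives, with the CGI) needs a trajectory or an improvement rating. CGI improvement is collected but not named as a target. Data management describes the gold standard as an assessment of the course, but for suicidality it uses the CGI-SS severity item, not the change item.
- Change (Discussion) needs a change score, a change rating or a within-patient contrast. None is named. The random intercepts in Tiers 1 and 2 deal with clustering. In the text models the fixed effects are only model size and temperature, so tracking of change is not tested.

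**2. The plan's own figure.** The sample size is an exact two-sided binomial test with p0 = 0.5 and p1 = 0.5 + 0.11 = 0.61. At n = 162 it reproduces exactly: critical values 68 and 94, alpha 0.0491726, power 0.8046757. It concerns one proportion and contains no parameter for change or prognosis.

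**3. How well a score blind to change could do.** The documents give no between-patient share of rating variance (ICC), so it is assumed. Let the rating be Y = u + e, with u the patient's stable level (variance ICC) and e the independent session deviation (variance 1 − ICC). Let the score equal u.
- Correlation with the same-session level: ICC / √ICC = √ICC.
- Change between sessions: Y(k+1) − Y(k) = e(k+1) − e(k). This contains no u, so the correlation is 0.
- AUC by simulation, 40,000 patients with five sessions each:

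| ICC (assumed) | r, level | AUC, top 20% | AUC, top 50% | r, change | AUC, worsening |
|---|---|---|---|---|---|
| 0.3 | 0.55 | 0.77 | 0.75 | 0.00 | 0.50 |
| 0.5 | 0.71 | 0.85 | 0.83 | 0.00 | 0.50 |
| 0.7 | 0.84 | 0.92 | 0.90 | 0.00 | 0.50 |
| 0.8 | 0.89 | 0.95 | 0.94 | 0.00 | 0.50 |

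**4. Prognosis and change need separate analyses.** In the same model, the partial correlation of u with Y(k+1) given Y(k) is √[ICC(1 − ICC) / (1 − ICC²)] = √[ICC / (1 + ICC)]. That is √(0.5/1.5) = 0.58 at ICC 0.5 and √(0.8/1.8) = 0.67 at ICC 0.8. A stable-level score would therefore pass a forward test adjusted for the current rating. That is real prognostic information, but it is still not tracking of change.

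**5. Consecutive pairs available.** Pairs = 200 interviews − number of patients.
- Two sessions each: 200 − 100 = 100. Three: 200 − 66.7 ≈ 133. Five: 200 − 40 = 160. One: 0.
- Sample size expects 15% to 20% loss. If only the recording at session k must be usable, multiply by 0.80 to 0.85: 80–85, 107–113 and 128–136 pairs.
- If both sessions must be usable and losses are independent, multiply by 0.80² = 0.64 to 0.85² = 0.72: 64–72, 85–96 and 102–116 pairs.

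**The case against.** **The protocol partly concedes the point.** The Discussion admits that long-term follow-up is lacking, speaks of insight into immediate risk, and leaves utility for tracking progress to future research. It also defers outcome prediction to a planned smartphone extension. This stands, and it would be wrong to say that only long-term follow-up is conceded. But the concession conflicts with the aim sentence in the same section, and short-term change from t1 to t5 is neither claimed nor excluded.

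**Change ratings are collected.** A reader might infer that every score is compared only with a same-session level. The documents do not support that. CGI improvement and CGI-SS change are recorded, and the generic reference to correlation with clinical measures could include them. What holds is narrower: no change item is named as a target.

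**The wording is soft.** The prognosis score is introduced as an example, the hypothesis belongs to an initial exploratory analysis, and predict can mean estimate in machine learning. That is fair for the score. It does not fit a sentence whose object is occurring changes.

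**Detail belongs in an analysis plan.** A reader might also infer that acoustic predictors are uncentred and that AUC pools sessions across patients. The article says neither, and such details may be fixed in a document not shown. The point does not depend on them. It concerns the targets the article does fix, in a framework it describes as preventing later flexibility.

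**The figures are a bound.** The text models are prompted zero-shot, and nothing suggests that they would know a patient's true level. The ICCs and class cuts are assumptions, and zero correlation with change holds by construction. All of this stands. The figures show what the planned measures cannot distinguish. They do not forecast this trial's results.

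**Conclusion.** The aims of prognosis, course and change are not matched by any analysis target that the article spells out. The contradiction can be read from the text and rests on no assumption. As written, the trial supports conclusions about concurrent detection of severity, suicidality and diagnosis. Those results remain valid for what they are.

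The illustrative size is an upper bound. Under normally distributed ratings with independent session deviations and an assumed ICC of 0.5 to 0.8, a score blind to change could show r of about 0.71 to 0.89 and AUC of about 0.85 to 0.95 for the top 20% of sessions. At ICC 0.3 the AUC is still 0.75 to 0.77, depending on the cut.

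A reader might go further and infer that a positive result will be reported as prognosis, or that the models will only separate patients. The documents support neither inference. The matter should be settled before analysis.

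**What to change.** **Reconcile the wording.** Call same-session results concurrent detection, rename the prognosis score accordingly, and bring the Objectives, Data management and the aim sentence of the Discussion into line with the Discussion's own limitation.

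**If prognosis or change claims are kept, pre-specify two analyses on data already scheduled:**
- (a) Forward: the speech or model score at session k against the rating at session k+1 (for example DSI-SS, BPRS or CGI), adjusted for the rating at k and the days between. Prognosis claims rest on this.
- (b) Within-patient change: use CGI improvement and CGI-SS change as targets, or split each predictor into the patient mean and the deviation from it and report the within-patient coefficient. Change claims rest on this. The CGI-SS appears in Table 2 but has no row in Table 1, so its timing should be stated.

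**Cost.** Wording and two extra models, with no new data. Patients with one session contribute to neither analysis that compares sessions. The 100 to 160 consecutive pairs are a ceiling for two to five sessions each, before the expected 15% to 20% loss. Participation ends when treatment is completed, so later sessions may be missing selectively, and this should be examined. Claims from same-session results become more modest.
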